### Secondary Outcomes

Difference in length of BPL and TSBL between the two groups.Changes in obesity-related diseases (diabetes, hypertension, dyslipidemia, sleep apnea) at 6 months and 1 year after OAGB. Remission of obesity-related diseases will be defined according to standard clinical criteria. In general, remission is considered when the patient is asymptomatic, no longer requires disease-specific medication, and relevant laboratory values are within normal limits. For example, type 2 diabetes remission will be defined as HbA1c < 6.5% without the use of antidiabetic medication, as per ADA criteria. Similar criteria will be applied for hypertension, dyslipidemia, and other obesity-related diseases, based on established clinical guidelines [16–18].Postoperative complications after OAGB—bile reflux, marginal ulcers, internal hernia, anastomotic strictures, and others—will be screened and compared.Incidence of nutritional complications (protein malnutrition, vitamin deficiencies) during the follow-up period.Changes in quality of life, as measured by the BAROS questionnaire at 6 months and 1 year post-surgery.

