The outcomes of patients after OAGB with a tailored BPL length are unclear. It is possible that these patients could have higher weight loss and metabolic outcomes. The purpose of this study is to evaluate if personalized tailoring of the BPL length to TSBL is effective and safe. Our primary outcome will investigate if tailored BPL is more effective in terms of percentage of total weight loss at 3 years compared to patients undergoing OAGB with a standard BPL length. We will also record perioperative and malnutrition-related outcomes in order to investigate the safety profile of the tailored BPL arm in comparison to the standard arm. We hypothesize that tailoring the BPL length to a percentage of the TSBL in patients undergoing OAGB will result in greater total weight loss after 1 and 3 years and result in comparable safety outcomes, including perioperative and malnutrition-related complications, compared to a fixed standard BPL length. We hereby present the protocol of the *T*ailored *B*iliopancreatic *L*imb *LE*ngth to 40% of TSBL study (TABLE-40 study).

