### Data Collection

Data will be collected prospectively at baseline, intra-operatively, and during follow-up visits.

The following data points will be collected:Demographics: Age, genderPre-operative: Weight, height, Body Mass Index (BMI), obesity-related conditions, previous abdominal surgeries, ASA score, Charlson comorbidity index (CCI), blood test results (hemoglobin, platelets, creatinine, albumin, vitamin D, B12, folic acid, iron, ferritin, transferrin, glucose, HbA1c, lipid profile, liver, thyroid and parathyroid function tests)Intra-operative: Date of surgery, duration of surgery, total small bowel length (cm), BPL length (cm), intra-operative complications.Post-operative: Post-operative complications (bleeding, leak, wound infection, VTE, surgical site infection), grading of complications according to Clavien-Dindo grading of complications [13], length of hospital stay, 90-day readmissions, 90-day reoperations.Follow-up (6 months, 1 year, 3 years): Weight, height, BMI, obesity-related conditions during follow-up, blood test results (as above), > 90-day complications, reoperations, quality of life measures will be measured according to the BAROS questionnaire [14]. Bowel habits and stool characteristics will be assessed according to the Fecal Score [15].

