### Follow-Up

Participants will be followed up at 2 weeks, 3 months, 6 months, 12 months, and annually thereafter. At each visit, weight, obesity-related diseases, and any complications will be assessed. Blood tests will be performed at 3–6 month intervals to monitor nutritional status.

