### Statistical Analysis

#### Sample Size

Based on the previous literature of study cohorts which are similar to our expected study population [21–23], our hypothesis is that at 3 years the tailored group will have a 5% higher %TWL in comparison to the fixed group (40% vs. 35%). In order to detect a difference in %TWL at 3 years with a power of 0.8 and an alpha significance of < 0.05 and standard deviations of 12, 90 patients are needed in each arm for a total of 180 patients. Assuming a drop-out rate of 10%, enrollment of 198 patients is needed for sufficient power for the trial.

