### Data Analysis

Statistical analysis will be performed using IBM SPSS Statistics software version 29. Continuous variables will be presented as means ± standard deviations, and categorical variables will be presented as frequencies and percentages. Baseline characteristics of the two groups will be compared using independent *t*-tests for continuous variables and chi-square tests for categorical variables.

The primary outcome (%TWL) will be compared between the two groups using an independent *t*-test. If data are not normally distributed, a Mann–Whitney *U* test will be used. Changes in obesity-related diseases and quality of life scores will be analyzed using paired *t*-tests or Wilcoxon signed-rank tests (as appropriate) to compare pre- and post-operative values within each group. Differences between groups will be assessed using independent *t*-tests or Mann–Whitney *U* tests. The incidence of complications will be compared between the two groups using chi-square tests or Fisher’s exact tests.

Multivariable regression analysis will be used to adjust for potential confounders (e.g., baseline BMI, comorbidities) in the analysis of the primary outcome. A *p*-value of < 0.05 will be considered statistically significant.

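### The only stated nutritional safety comparison is a yes/no incidence, although the markers are collected as continuous values; a baseline-adjusted comparison of the values should be added alongside it

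*Protocol article*

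**What the plan says.** The protocol article, Secondary Outcomes, lists one nutritional outcome: "Incidence of nutritional complications (protein malnutrition, vitamin deficiencies) during the follow-up period". Under Data Analysis, "The incidence of complications will be compared between the two groups using chi-square tests or Fisher’s exact tests". The same section assigns t-tests or Mann–Whitney tests to %TWL, and paired and between-group tests on the continuous scale to obesity-related diseases and quality of life. Nutritional values are not mentioned there.

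Data Collection lists the preoperative laboratory panel, "blood test results (hemoglobin, platelets, creatinine, albumin, vitamin D, B12, folic acid, iron, ferritin, transferrin, glucose" and others, and repeats it afterwards: "Follow-up (6 months, 1 year, 3 years): Weight, height, BMI, obesity-related conditions during follow-up, blood test results (as above". The Follow-Up section adds "Blood tests will be performed at 3–6 month intervals to monitor nutritional status".

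The Introduction makes nutritional safety part of the hypothesis. The tailored limb is expected to "result in comparable safety outcomes, including perioperative and malnutrition-related complications, compared to a fixed standard BPL length". No cut-off for any deficiency, expected rate, effect size or power is given for this outcome.

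**The concern.** A vitamin deficiency is ordinarily a cut on a measured level. Analysing only whether the cut was crossed discards how far levels moved, and it discards the preoperative value of the same marker, which the trial also holds.

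This matters more here than for a routine secondary outcome, for two reasons. The review summarised in the Introduction found that limb length bears more on the risk of nutritional deficiency than on weight loss. And, by the protocol's own rules, the tailored limb is never shorter than the control limb: with small bowel length of at least 450 cm, 0.40 × 450 = 180 cm. Any nutritional effect therefore has an expected direction. If deficiencies are uncommon, a general downward shift in levels could pass unseen in a comparison of rates, although the data to show it would already be in hand.

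**Working it through.** **The plan's own figure.** The Sample Size section states "power of 0.8 and an alpha significance of < 0.05 and standard deviations of 12, 90 patients are needed in each arm", for 40% against 35% TWL. The standardised effect is 5/12 = 0.417. At 80% power and two-sided 5% this needs 91 per arm against 90 stated, and 90 per arm gives about 80% power. The figure reproduces. It concerns %TWL only.

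**Inputs for the nutritional comparison.** From the article: 90 analysed per arm, and alpha 0.05 (taken as two-sided). Assumed, because the article gives nothing: a normally distributed marker, a uniform downward shift d of 0.3, 0.4 or 0.5 SD in the tailored arm (bracketing 0.417), and a control deficiency rate p of 5, 10, 20 or 30% per visit.

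**One visit.** Tailored rate = Φ(Φ⁻¹(p) + d). For p = 5% and d = 0.4: Φ(−1.645 + 0.4) = 10.7%. Power of the uncorrected chi-square test was found by exact enumeration. Power of the t-test uses the noncentral t with noncentrality d√(90/2), which is 2.68 for d = 0.4.

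| d | t-test | Chi-square at p = 5 / 10 / 20 / 30% | Gap in points (from unrounded powers) |
|---|---|---|---|
| 0.3 | 51.7% | 16.9 / 23.8 / 30.9 / 35.0% | 34.7 / 27.8 / 20.8 / 16.7 |
| 0.4 | 76.1% | 28.9 / 39.6 / 50.6 / 56.1% | 47.2 / 36.4 / 25.5 / 20.0 |
| 0.5 | 91.6% | 44.6 / 58.2 / 70.4 / 75.4% | 47.0 / 33.4 / 21.1 / 16.1 |

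The gap is about 16 to 47 points. Fisher's exact test loses roughly a further 5 to 8 points at these rates. Adjusting for a baseline value correlated 0.5 with follow-up raises the effective shift to d/√(1 − 0.25). For d = 0.4 that is 0.462, and power is 86.9%.

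**Three visits.** The stated outcome is incidence over follow-up, so a single visit does not match it. Take ever-deficient over 6, 12 and 36 months, with within-person correlation 0.5 (assumed). Control rates become 11.8, 21.8, 38.9 and 53.0%. The like-for-like continuous comparison is the mean of the three values. Its SD is √((1 + 2 × 0.5)/3) = 0.816, so d becomes d/0.816.

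| d | t-test on mean of three | Chi-square, ever deficient, at p = 5 / 10 / 20 / 30% | Gap in points |
|---|---|---|---|
| 0.3 | 68.8% | 30.7 / 38.9 / 42.6 / 44.3% | 38.1 / 29.9 / 26.2 / 24.6 |
| 0.4 | 90.5% | 51.1 / 61.9 / 65.9 / 67.4% | 39.3 / 28.5 / 24.6 / 23.1 |
| 0.5 | 98.3% | 72.0 / 81.6 / 84.5 / 84.7% | 26.3 / 16.7 / 13.9 / 13.7 |

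The gap is about 14 to 39 points.

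**Harm confined to a minority.** Let 10% of tailored patients shift by 2 SD and the rest not at all, at one visit with p = 5%. Tailored rate = 0.9 × 5% + 0.1 × Φ(−1.645 + 2) = 10.9%. The mean shift is only 0.2 SD and the tailored variance is 1 + 0.1 × 0.9 × 4 = 1.36, so SE = √(2.36/90) = 0.162. Power is 31% for the rate and Φ(0.2/0.162 − 1.96) = 23% for the mean. The order has reversed.

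**The case against.** Several objections carry weight.

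*Incidence accumulates.* Repeated testing raises the power of the yes/no comparison: for d = 0.4 and p = 5% it goes from 29% at one visit to 51% over three. Against the one-visit t-test (76%) the gap would fall from 47 to 25 points. But that gives the repeated measurements to one side only. With both sides using three visits the gap is 39 points. The objection shows that the one-visit range is not the figure for the stated outcome; it does not remove the loss.

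*Harm may be concentrated.* The tailored limb equals the control limb at 450 cm and lengthens with bowel length, so a uniform shift is not assured. The reversal above is real. It is a reason to keep the incidence test.

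*Deficiency is the clinical event.* This stands too. A mean difference within the normal range answers a different question, and supplements given for a low value can shrink differences in levels.

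*The cut is partly inferred.* Protein malnutrition may be a clinical diagnosis; the article does not tie it to an albumin threshold. Ferritin is measured but is not part of the stated outcome. The dichotomising is clearest for vitamin D, B12 and folic acid.

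*An analysis plan may cover it.* The plan is not shown and may add models for laboratory values; nothing in the article forbids them. But the article does more than stay silent: it fixes the outcome as an incidence and names a test for it. The point rests on that stated choice.

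**Conclusion.** The concern holds in a limited form. As written, the nutritional safety comparison uses only a yes/no incidence, while continuous values with their own baseline are collected and given no between-arm comparison. Under a uniform normal shift of 0.3 to 0.5 SD, 90 per arm and control rates of 5 to 30% per visit, this costs about 16 to 47 points of power at one visit, or about 14 to 39 points over three visits at correlation 0.5.

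A reader might infer three stronger things, and the documents support none of them. The first is that these ranges are properties of this trial: the article gives no rates, spread or effect for any marker. The second is that the continuous comparison is always better: it is not when harm sits in a small subgroup. The third is that incidence is the wrong outcome and should become merely descriptive: it is a meaningful safety event and matches the hypothesis as worded.

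The primary analysis and sample size are unaffected. This is a worthwhile improvement to a secondary safety analysis.

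**What to change.** Keep the between-arm test of deficiency incidence as stated. Add to Secondary Outcomes and Data Analysis a between-arm comparison of continuous albumin, vitamin D, B12 and folic acid, on the log scale where skewed. Use ANCOVA, or a repeated-measures model over 6, 12 and 36 months, adjusted for the preoperative value of the same marker. Report mean differences (ratios for logged markers) with 95% confidence intervals, labelled as supportive safety estimates so that the extra comparisons are not read as separate confirmatory tests.

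The cost is a few sentences and a few extra models on data already planned. The downsides are small: more comparisons to report, and level differences that supplementation may blunt, which the report should say.

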### Quality of Life Measures

#### MA-II Questionnaire

We will use the Moorehead-Ardelt Quality of Life Questionnaire II (MA-II), which is part of the Bariatric Analysis and Reporting Outcome System (BAROS), to assess quality of life at 6, 12 and 36 months postoperatively. The BAROS system was originally introduced in the 1990 s and was updated in 2009. The revised MA-II includes six questions evaluating self-esteem, physical activity, social life, work conditions, sexual activity, and the individual’s relationship with food. All six questions are equally weighted, with each item assigned a score of 0.5 points. A 10-point Likert-type scale is now utilized in the scoring system. As in the original BAROS questionnaire, the updated version maintains a weighted structure, with a central neutral value of 0 and positive or negative changes represented to the right and left, respectively.

Based on the final score, outcomes are categorized into five groups: failure (≤ 0), fair (0.1–1.5), good (1.6–3.0), very good (3.1–4.5), and excellent (4.6–6.0 points).

### Fecal Score (FS)

Altered bowel habits—such as loose stools, increased frequency of defecation, and even fecal incontinence—can significantly impact quality of life following bariatric surgery. To evaluate these changes, we are using the semi-quantitative Stool Frequency and Consistency Score, also known as the Fecal Score (FS), to assess bowel movement patterns at 6, 12, and 36 months postoperatively. The FS (Fecal Score) is calculated based on three components: fecal frequency, fecal consistency, and the impact on quality of life. Fecal frequency is assessed using a 5-point scale: less than twice per week (1 point), every two days (2 points), once daily (3 points), twice daily (4 points), and more than twice daily (5 points). Fecal consistency is also scored on a 5-point scale: watery stools (5 points), loose stools (4 points), normal stools (3 points), firm stools (2 points), and hard stools associated with constipation (1 point). The impact on quality of life due to frequent bowel movements is also rated on a 5-point scale, where 1 point indicates no impact, 2 points indicate mild impact such as anxiety related to bowel habits, 3 points indicate moderate impact including the use of aids (e.g., sanitary pads) due to occasional fecal leakage, 4 points indicate severe impact requiring restriction to locations near restrooms, and 5 points reflect very severe impact, including avoidance of leaving the house. The total FS ranges from 3 to 15, with higher scores indicating more frequent, looser stools and greater impact on daily functioning.

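### The Fecal Score is adopted to evaluate changes in bowel habit but is never taken before surgery, so within-patient change and new-onset symptoms cannot be reported and some precision is lost; it is also not named among the secondary outcomes.

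*Protocol article*

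**What the plan says.** The section Fecal Score (FS) opens by naming loose stools, more frequent defecation and fecal incontinence as consequences of bariatric surgery that can affect quality of life. It then gives the purpose of the instrument: "To evaluate these changes, we are using the semi-quantitative Stool Frequency and Consistency Score". The timing follows in the same sentence: "to assess bowel movement patterns at 6, 12, and 36 months postoperatively". The score has three items (frequency, consistency, impact on quality of life), each rated 1 to 5, for a total of 3 to 15.

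The Data Collection section matches this. The statement "Bowel habits and stool characteristics will be assessed according to the Fecal Score" stands inside the follow-up item, which begins "Follow-up (6 months, 1 year, 3 years): Weight, height, BMI". The separate pre-operative item begins "Weight, height, Body Mass Index (BMI), obesity-related conditions, previous abdominal surgeries, ASA score" and goes on to the Charlson index and a long blood panel. It contains no stool or bowel-habit entry.

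The Secondary Outcomes section covers limb and bowel length, obesity-related diseases, postoperative complications, nutritional complications and quality of life. Its quality-of-life entry is "Changes in quality of life, as measured by the BAROS questionnaire at 6 months and 1 year post-surgery". The Fecal Score is not named there.

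**The concern.** An instrument brought in to evaluate a change has no value from before the change. A patient with a high score at 6 months may have been changed by the operation or may have had that bowel habit already, and the planned data cannot tell the two apart. A pre-operative score also cannot be collected prospectively once the patient has been operated on.

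The measure matters in this comparison. Patients with a total small bowel length below 450 cm are excluded, and 40% of 450 cm is 180 cm. The tailored limb is therefore never shorter than the fixed one and is longer whenever the bowel exceeds 450 cm. The abstract undertakes to check that the approach does not harm quality of life, and the Fecal Score section itself links bowel habit to quality of life. A potential harm described in such detail would be expected to have a starting value and a named place among the outcomes.

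**Working it through.** **Step 1. Is there a pre-operative score anywhere?** The article touches on the score's timing or status in these places:

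| Place in the protocol article | What it gives for the Fecal Score |
|---|---|
| Fecal Score (FS) | 6, 12 and 36 months after surgery |
| Data Collection, follow-up item | 6 months, 1 year, 3 years |
| Data Collection, pre-operative item | not listed |
| Primary Outcome | not the score (%TWL) |
| Secondary Outcomes | not listed |

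The two schedules agree with each other and neither has a pre-operative time point. The pre-operative list is itemised, so the absence is not simply a product of condensing.

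**Step 2. What can still be estimated?** Allocation is random, so pre-operative bowel habit has the same expected distribution in both arms. The difference between arms in post-operative scores at 6, 12 or 36 months is an unbiased estimate of the effect of limb strategy. Three things cannot be obtained: a patient's change from before surgery, the proportion with newly arising symptoms, and an arm comparison adjusted for the pre-operative score.

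**Step 3. How much precision is at stake?**

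Inputs:
- Patients per arm: 90, from Sample Size. That figure is for %TWL and reproduces: 2 × [12 × (1.960 + 0.842) / 5]² = 90.4. It serves here only as the number analysed.
- Two-sided 0.05 and power 0.80. The article gives 0.05 and 0.8; two-sided is assumed.
- Correlation r between pre-operative and follow-up scores: not in the documents. Assumed 0.1 to 0.5.
- Standard deviation of the score: not in the documents, so differences are expressed in SD units.

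Formulas:
- Residual variance after adjustment, as a fraction of the unadjusted variance: 1 − r².
- Equivalent gain in sample size: 1/(1 − r²) − 1.
- Detectable difference without a baseline: √(2/90) × (1.960 + 0.842) = 0.418 SD. With adjustment, multiply by √(1 − r²).
- Power for an illustrative true difference of 0.4 SD (also an assumption), by t-test with the effect scaled by 1/√(1 − r²).

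| Assumed r | 1 − r² | Equivalent sample gain | Detectable difference (SD) | Power at 0.4 SD |
|---|---|---|---|---|
| no baseline | 1.00 | none | 0.418 | 0.76 |
| 0.1 | 0.99 | 1.0% | 0.416 | 0.76 |
| 0.2 | 0.96 | 4.2% | 0.409 | 0.78 |
| 0.3 | 0.91 | 9.9% | 0.398 | 0.80 |
| 0.5 | 0.75 | 33.3% | 0.362 | 0.87 |

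The operation itself alters bowel habit, which may weaken the correlation over 36 months, so the low rows are as plausible as the high ones. In those rows the gain in precision is negligible, and the main benefit of a pre-operative score is being able to describe change and new onset.

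**The case against.** The strongest reply is that a randomised trial does not need a baseline to compare arms. That stands. A reader might infer that the stool effect of the longer limb cannot be estimated, or that chance imbalance in pre-operative bowel habit would distort it. Neither follows: the comparison is unbiased, and chance imbalance is ordinary sampling variation already reflected in the standard error.

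A second reply is that the text does not contradict itself. The changes it speaks of can be read as the bowel habits seen after bariatric surgery in general, and what is actually planned is a description of post-operative patterns. No change score is promised for this instrument. This also stands, so the point is a gap between stated purpose and schedule, not a conflict between two passages.

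Third, the missing outcome label may be partly layout. The Fecal Score section follows the outcome and quality-of-life sections, defines its scoring and time points in full, and includes an item on quality of life. A reader might infer that the score is shut out of the safety and quality-of-life conclusion because it is not listed. No part of the article limits that conclusion to listed outcomes. The remedy here is a labelling clarification.

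Fourth, a reader might object that Data Analysis names no test for the score. Choosing a test for each non-primary measure is commonly left to a statistical analysis plan, which is not shown, so nothing is claimed on that ground.

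Finally, the precision figures rest on assumed correlations and an assumed 0.4 SD difference. That is true, which is why the range is shown down to a gain of 1%.

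**Conclusion.** The point holds in limited form. No pre-operative Fecal Score is scheduled in either place that sets its timing, and the score is not named as a secondary outcome, although it is introduced to evaluate change. The consequence is that within-patient change and new-onset symptoms cannot be reported and pre-existing symptoms cannot be separated from new ones. In addition, the arm comparison gives up precision worth about 1% to 33% of the sample size, if the correlation lies between 0.1 and 0.5. The validity of the between-arm comparison, the primary outcome and the sample size are not affected. This is a cheap improvement to a safety-related measure, not a flaw in the trial's main inference. Its urgency comes only from the fact that the missing value cannot be recovered after surgery.

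**What to change.** 1. **Data Collection, pre-operative item:** add the three-item Fecal Score, completed at a pre-operative appointment that already takes place.
2. **Secondary Outcomes:** list the Fecal Score, using the protocol's own 3 to 15 total, at 6, 12 and 36 months.
3. **Analysis of the score:** compare the arms adjusted for the pre-operative score, here or in the statistical analysis plan. Change from before surgery and new-onset symptoms can then be described by arm.

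The cost is a minor amendment and three extra questions per patient. Patients operated on before the change will have no pre-operative score. They can stay in the arm comparison with a missing-baseline indicator, but cannot contribute to the description of change.

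If a pre-operative score is not wanted, the least that is needed is to reword the purpose as a between-arm comparison of post-operative bowel habit and to list the score among the secondary outcomes.

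### The Fecal Score total is not ordered from good to bad, so bowel tolerability should be read from its three components as well as from the total

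*Protocol article*

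**What the plan says.** The Fecal Score section of the protocol article describes a score "calculated based on three components: fecal frequency, fecal consistency, and the impact on quality of life".

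- **Frequency:** the lower levels are "less than twice per week (1 point), every two days (2 points), once daily (3 points"); the upper levels are "twice daily (4 points), and more than twice daily (5 points").
- **Consistency:** watery scores 5 and loose scores 4, followed by "normal stools (3 points), firm stools (2 points), and hard stools associated with constipation (1 point").
- **Impact:** "The impact on quality of life due to frequent bowel movements is also rated on a 5-point scale, where 1 point indicates no impact". Level 3 involves occasional leakage with use of aids, level 4 is severe (staying near a toilet), and level 5 is not leaving home.

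The only interpretation offered is for the sum: "The total FS ranges from 3 to 15, with higher scores indicating more frequent, looser stools and greater impact on daily functioning". The article gives no normal value and no cut-off. The score is taken at 6, 12 and 36 months, and no baseline measurement is stated.

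The score appears under Data Collection and in its own section. It is not among the Secondary Outcomes, and Data Analysis does not name it. That section gives between-group t-tests or Mann–Whitney tests for obesity-related diseases and quality of life scores.

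**The concern.** The sum mixes two kinds of item. Frequency and consistency depart from normal in two directions, while impact departs in one. Adding them gives a total whose lowest value belongs to a constipated patient and not to one with normal habit. The impact item is tied to frequent motions, so burden caused by constipation has no place in the score.

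A difference between arms in mean or median total is then ambiguous. It could mean more diarrhoea, less constipation or more impact, or it could be the remainder after opposite shifts have partly cancelled.

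This matters because the Abstract sets out to make sure that the tailored approach does not worsen quality of life, and the Fecal Score section itself names loose, frequent stools and incontinence as the worry. The tailored limb is never shorter than the control limb, so bowel tolerability is a question on which the arms could plausibly differ. Of the instruments that the article describes, this is the one that grades leakage and restriction to places near a toilet.

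**Working it through.** **Inputs** (Fecal Score section unless noted): three items, each 1 to 5; once daily = 3 and normal stool = 3; less than twice weekly = 1 and hard stool with constipation = 1; watery = 5 and more than twice daily = 5; impact 1 = none, 4 = severe, 5 = very severe. From the Intervention section and Table 1: tailored limb 40% of total small bowel length, control limb 180 cm, and exclusion below 450 cm.

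**Stated range.** Minimum 1+1+1 = 3 and maximum 5+5+5 = 15. This reproduces the stated 3 to 15; the midpoint is (3+15)/2 = 9.

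**Reference profiles** (frequency + consistency + impact):

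| Profile | Sum | Total |
|---|---|---|
| Constipation, no impact recorded | 1+1+1 | 3 |
| Normal habit | 3+3+1 | 7 |
| Watery, more than twice daily, no impact | 5+5+1 | 11 |
| Worst on every item | 5+5+5 | 15 |

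Constipated versus normal is a gap of 7 − 3 = 4. Normal versus watery and frequent is 11 − 7 = 4. The total gives both gaps the same size and sign.

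**One difference, three explanations.** Take an arm in which everyone else is at 7. Each of these contrasts moves the mean by 0.8:

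- 10% of patients at 15 instead of 7: 0.10 × (15 − 7) = 0.8
- 20% at 11 instead of 7: 0.20 × (11 − 7) = 0.8
- 20% in the *other* arm at 3 instead of 7: 0.20 × (7 − 3) = 0.8

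The first two are more diarrhoea; the third is less constipation.

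**Cancellation.** An arm with 10% at 15, 20% at 3 and 70% at 7 has mean 0.10 × 15 + 0.20 × 3 + 0.70 × 7 = 1.5 + 0.6 + 4.9 = 7.0, the same as an arm with normal habit throughout. These shares are illustrative; the article gives no rates.

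**Same total, different burden.** No-impact totals run from 1+1+1 = 3 to 5+5+1 = 11. To keep the profiles consistent with an impact item about frequent motions, restrict raised impact to patients with at least two motions daily and normal or looser stools. Severe impact then starts at 4+3+4 = 11, which ties with 5+5+1 = 11. A total of 11 can therefore be a patient with no impact or one with severe impact.

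**Relevance to the arms.** The shortest tailored limb is 0.40 × 450 = 180 cm, equal to control. At 600 cm it is 0.40 × 600 = 240 cm, and at 800 cm it is 0.40 × 800 = 320 cm.

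**The case against.** The strongest reply is that no stated analysis is at fault. Data Analysis does not name the Fecal Score, and how a measure outside the outcome list is tabulated is a detail that an article may leave to a fuller document. The score also comes from a cited source, so its coding is inherited. And for the harm the trial has in mind, looser and more frequent stools with more restriction, every item pushes the total upward, which is the right direction. All of this stands and limits the point to a risk of misreading. It does not remove that risk, because the sum is the only quantity the article interprets, and the arithmetic follows from the printed scoring whatever its source.

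Full masking also takes a contrived mix. An arm split evenly between 3 and 11 would have mean (3+11)/2 = 7, but every patient would lie 4 points from it, so a reported standard deviation of about 4 would expose the pattern. Partial cancellation is the more realistic worry.

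A reader might infer more than the document supports:

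- *That normal habit sits at the middle of the total.* It does so on the frequency and consistency items only; the total is 7 against a midpoint of 9.
- *That the protocol treats low totals as favourable.* The text gives a direction and never calls a low score good.
- *That one total can mean no impact or being housebound.* The sum 3+3+5 = 11 is possible on paper, but it describes once-daily normal stools in someone housebound by frequent motions. If either stool item must be raised and neither may fall below normal, the housebound minimum is 4+3+5 = 12 and the overlap with the no-impact maximum of 11 disappears. The tie with severe impact is the coherent one.
- *That absence from Secondary Outcomes shows the score is flawed.* That is a separate listing matter.

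**Conclusion.** The point holds as a risk to interpretation. The total is not monotone from good to bad (3 constipated, 7 normal, 11 watery and frequent without impact), and the statement that a higher total means greater impact on daily functioning does not always hold, as 5+5+1 and 4+3+4 show. Taken alone, a difference in mean totals cannot distinguish less constipation from more harm, and opposite shifts can partly cancel.

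How much this would matter depends on the share of constipated patients in each arm, which the article does not give. If constipation is rare in both arms, the total will track diarrhoea reasonably well; the ambiguity grows as the share rises or differs between arms. With no baseline score stated, pre-existing constipation cannot be separated from an effect of surgery within a patient. The conclusion rests only on the printed item scoring and on the total being a plain sum, which the stated range of 3 to 15 confirms.

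**What to change.** Keep the Fecal Score total at 6, 12 and 36 months. At the same visits, also compare the arms on the three components (frequency, consistency and impact) as ordinal distributions over the five levels. Show separately by arm the proportions with loose or watery stools (consistency 4 or 5), with constipation (consistency 1) and with impact of 3 or more. State that tolerability will be read from the components and not from the total alone.

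The proportions are for presentation. Formal tests on these cut-offs are optional: dichotomising loses sensitivity, and the cut-offs need not replace the total or the ordinal comparisons.

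The cost is a few sentences, a few extra tables and some additional comparisons without multiplicity adjustment, to be labelled as such. No new data are needed, because all three items are already recorded at every one of these visits. Writing this down before results by arm are seen also prevents later selection among the items.
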